### Further Study Details

All participants will complete a written informed consent for this voluntary study. Participants will be able to withdraw from TECC anytime, just as they can withdraw from routine care at any time. Participants who miss four consecutive sessions will be asked to restart the protocol. During the study, if a participant’s clinical presentation significantly worsens, the clinical team will re-evaluate the participant’s involvement in the study. Intent-to-treat analysis will be applied so that data from all participants, even those who drop out, will be included in the outcomes.

The mindLAMP app meets federal privacy and security requirements, and has been institutional review board (IRB)–approved for use in clinical research. All data collected by mindLAMP will be securely transmitted directly to a server within the hospital network. Additionally, after receiving IRB approval, the TECC protocol will be registered with ClinicalTrials.gov.

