Furthermore, TECC seeks to balance clinician and participant autonomy while providing some structure and treatment pathways. Thus, the protocol was specifically designed to empower clinicians and participants to use smartphone technology by customizing data collection of both mental health surveys as well as sensor data (if agreed upon) toward ensuring each participant’s unique experience is captured. Although each session of the protocol offers exercises related to aspects of the app, which the participant should complete between sessions, these activities are defined broadly to meet diverse clinical needs and offer clinicians therapeutic flexibility. For example, using the app toward goal setting and tracking will be applicable in almost any scenario.

The eight-session structure included in TECC will provide the flexibility for clients to learn about different treatment modalities to gain broad exposure to evidence-based therapeutic skills and techniques while still ensuring treatment is focused on personal needs. The clinical skills incorporated in TECC were chosen from current research done on short-term mental health treatments, studies designed specifically to understand marginalized communities, and app-based mental health interventions. The protocol consists of three main stages:

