### Study Measures

Since TECC was designed to collect a number of clinical surveys throughout treatment, the timeline for survey collection was carefully crafted to decrease oversaturation (see Figure 2 for survey timeline). Specifically, participants will be asked to complete the PHQ-9 (which measures depression rates from minimal depression to severe depression) and the GAD-7 scale (a widely accepted anxiety scale that evaluates scores as either mild, moderate, or severe anxiety) on a daily basis [46,47]. Both the PHQ-9 and GAD-7 scales will be loaded on mindLAMP and become available to participants upon downloading.

Prior to each clinical visit, participants will briefly meet with a research assistant who will provide participants with a secure link (via REDCap) to weekly clinical surveys. This could be done via mindLAMP, but we will use a different platform for the purposes of this study. Those presession surveys include the Sheehan Disability Scale, which measures the effects of poor mental health across three domains: work and school, family, and social life [48]; the Primary Care Posttraumatic Stress Disorder-5, which assess for posttraumatic stress disorder [49]; the Behavior and Symptom Identification Scale-24, a symptom assessment scale [50]; a patient motivation scale, to asses participants commitment to change through treatment; the World Health Organization Five, a well-being assessment scale [51]; and the Working Alliance Inventory–Short Form, a scale to assess the alliance a patient feels toward the clinician that is known to be a predictor of treatment success (this scale will begin after session one) [52].

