### Analysis

Analysis will include calculation of the effect size of TECC to reduce symptoms related to stress, anxiety, and depression. Analysis will also focus on assessing association between baseline factors, race, language, and education, as well as dynamic factors like working alliance and technology engagement patterns with changes in symptoms and use and adherence to the TECC protocol. We will assess relationships between these factors and clinical changes using generalized linear models and multiple regression analyses. Tests for dropout effects will be performed to see if outcome and covariate measures are associated with differences in engagement. If there are significant dropout effects, a logistic dropout probability model will be fit using the significant dropout outcomes and covariates measured at the start of the stage, and inverse probability weighting will be used with these model probabilities to account for dropout in each of the models. The age-matched control group will be used to compare changes related to clinical scores and calculate effect sizes using means and SDs.

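### The intent-to-treat promise and the start-of-stage dropout weights are not reconciled for participants who leave because they worsen

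*Protocol article*

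**What the plan says.** Two places in the protocol article bear on this point.

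- **Methods, Further Study Details.** If a participant's "clinical presentation significantly worsens, the clinical team will re-evaluate" that person's involvement. Removal is a possible result but is not stated as automatic, and no threshold is given. The next sentence reads: "Intent-to-treat analysis will be applied so that data from all participants, even those who drop out, will be included in the outcomes".
- **Results, Analysis.** There is one dropout method, whatever the reason for leaving. Dropout effects are tested first, and the adjustment follows only when that test is significant. For the model behind the adjustment, the article says that "a logistic dropout probability model will be fit using the significant dropout outcomes and covariates measured at the start of the stage". The fitted probabilities are then turned into weights, which apply to every model in the analysis.

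Three other statements set the frame. The Introduction says "The protocol consists of three main stages", and I take these to be the stages that the Analysis section means. It also defines response as a 50% reduction in symptoms. Study Measures has PHQ-9 and GAD-7 completed every day in the app. On the outcome, the Analysis section says "Analysis will include calculation of the effect size of TECC to reduce symptoms related to stress, anxiety, and depression".

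**The concern.** Continued participation may depend on the outcome itself. Someone whose depression or anxiety score climbs during a stage is the person whose involvement is reconsidered. If that person leaves, the reason is a change that took place after the stage began. A weight built from start-of-stage values cannot see that change. It lets a participant who began the stage alike, but did not worsen, stand in for the one who left.

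The intent-to-treat sentence points the other way, since data from people who leave are to be included. It does not say which value represents them at the end, and the weighting is the only operational method given. The two readings lead to different results: one keeps the worsened scores, the other can replace them with the scores of people who did better. At stake are the mean change, the effect size and the response rate. The comparison with the matched cohort may also be affected, because the article describes no similar re-evaluation for that cohort.

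**Working it through.** The article gives no removal rate, worsening threshold or SD, so there is no stated figure to reproduce. The check has two parts.

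**1. What the weights can contain.** The treatment is described as 8 weeks in three stages, so a stage averages 8 × 7 / 3 ≈ 19 days, and longer if the eight sessions spread over the permitted 2 to 4 months. The dropout model uses outcomes as well as covariates and is tied to stages, so worsening in an earlier stage can enter. Worsening since the current stage began cannot enter, although daily scores record it.

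**2. Direction and size, by simulation.** All inputs here are assumptions except the three stages and the 50% response definition:

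- baseline PHQ-9 normal, mean 11, SD 3;
- mean change −1.5 per stage, with a 0.2 pull towards the mean and random SD 2.5 or 3.5 per stage;
- exit with probability 0.5 or 0.9 if the score rises by at least 2 or at least 3 points within the stage;
- 400,000 simulated participants per scenario.

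The true value is the mean change in everyone, had all been followed to the end. It is compared with (a) those who remain, unweighted; (b) those who remain, weighted by the inverse of a logistic probability from baseline and start-of-stage scores; and (c) everyone, using the last score up to exit. Overstatement is the size of (b) minus the size of the true change.

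| SD; rise; prob. | Left | True | (a) Remain | (b) Weighted | Overstated | (c) Last score |
|---|---|---|---|---|---|---|
| 2.5; 3; 0.5 | 6.1% | −4.50 | −4.76 | −4.77 | 0.27 | −4.36 |
| 2.5; 3; 0.9 | 11.0% | −4.50 | −5.00 | −5.01 | 0.51 | −4.26 |
| 2.5; 2; 0.5 | 12.9% | −4.49 | −4.99 | −5.00 | 0.51 | −4.22 |
| 3.5; 3; 0.5 | 15.3% | −4.51 | −5.27 | −5.34 | 0.83 | −4.14 |
| 2.5; 2; 0.9 | 22.8% | −4.50 | −5.46 | −5.49 | 0.99 | −4.01 |
| 3.5; 2; 0.5 | 23.3% | −4.52 | −5.59 | −5.69 | 1.16 | −3.97 |
| 3.5; 3; 0.9 | 26.8% | −4.50 | −5.97 | −6.11 | 1.61 | −3.83 |
| 3.5; 2; 0.9 | 40.2% | −4.50 | −6.68 | −6.87 | 2.37 | −3.52 |

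In every row the weighted result is no closer to the truth than the unweighted one.

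Response behaves the same way. At 6.1% leaving, it is 41.5% weighted against a true 39.0%. At 40.2% leaving, it is 61.3% against 42.0%. Counting those who left as non-responders gives 38.5% and 34.8% in these two rows, which errs on the low side.

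A second set of assumptions (baseline SD 2.5, certain exit on a rise of 3 or more, stage SD 2.5, 3.0 or 3.5) gives the same direction:

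- 10.3% leaving: 5.12 − 4.50 = 0.62 points
- 18.7% leaving: 5.74 − 4.49 = 1.25 points
- 27.0% leaving: 6.52 − 4.48 = 2.04 points

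At about 27% leaving, the two sets give 1.61 and 2.04, so the size depends on more than the number who leave.

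**The trigger.** With 50 participants, 10% leaving is 50 × 0.10 = 5 people. A significance test on five exits may well miss the effect, and then no weighting is applied. Column (a) shows that an unweighted analysis of those who remain carries nearly the same bias.

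**The case against.** The strongest reply is the intent-to-treat sentence itself. It directly follows the re-evaluation rule and promises that data from those who drop out are included. Scores are collected daily, so a worsening can be on record before any exit. If those scores are used, column (c) shows a change of −3.5 to −4.4 against a true −4.5, with no overstatement. This stands, and it rules out a stronger reading that a reader might reach: that participants who worsen are taken out and their harm is deleted from the result. The article says that involvement is re-evaluated. It states no automatic removal and nowhere says that scores are discarded.

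A reader might also infer that worsening is captured nowhere because response counts only improvement. The article does not support that either. Mean change is signed, so a worsened score that is kept lowers it. A separate count of those who deteriorate would be a reporting preference. Nor does the weighting apply to everyone who leaves, since it depends on a significant test.

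It can further be said that a condensed article may leave estimation detail to an analysis plan. That is fair for the choice of value for a leaver. It does not cover the timing of the weights, because the article itself fixes the start of the stage, and that choice cannot account for exits caused by what happens later in the stage.

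**Conclusion.** The point holds in a conditional form. The intent-to-treat promise and the start-of-stage weighting are not reconciled for participants who leave because they worsen. If an analysis of those who remain governs the result, weighted or unweighted, it is biased towards benefit. If recorded scores up to exit are kept for everyone, it is not.

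The direction is secure for exits driven by within-stage worsening. The size is not derivable from the article. The range of about 0.3 PHQ-9 points (6% leaving) to about 2.4 points (40% leaving) rests wholly on the assumed scores, variation and exit rule. In a study of 50, the low end concerns about 50 × 0.061 ≈ 3 people and the high end about 50 × 0.402 ≈ 20. If few leave for this reason, the effect is small. No view is taken on the clinical re-evaluation rule.

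**What to change.** In the Analysis section:

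1. State that all PHQ-9 and GAD-7 scores recorded up to exit stay in the change analysis, so that the intent-to-treat promise has a defined meaning for those who leave.
2. Use the latest daily scores before exit in the dropout model, rather than only start-of-stage values.
3. Record withdrawal for worsening as a reason of its own, apart from voluntary dropout.
4. Count these participants as non-responders in the 50% response analysis, at least as a sensitivity analysis.

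Item 2 cannot replace item 1. If half of those who worsen leave, each one who stays carries a weight of 1 / (1 − 0.5) = 2. If nine in ten leave, it is 1 / (1 − 0.9) = 10. If all leave, nobody remains to be weighted up.

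The cost is one reason code, some wording and slightly more analysis, using scores that are already collected. The response rate and effect size become somewhat conservative, as column (c) and the non-responder figures show. Continuing the surveys after exit would help further, but that would be new data collection and is not needed for this correction.

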## Results

The results of the TECC study will be used to support or adapt this model of care and create training resources to ensure its dissemination. The 1-year study timeline for TECC includes continuous recruitment and enrollment efforts until the sample size is reached; 10 months of clinical sessions, continuous collection of data, and in-session review of clinical metrics; several months spent analyzing data; and dissemination of study results (see Figure 10 for details).

**Figure 10 figure10:**
[figure not shown]
Study timeline. TECC: Technology Enabled Clinical Care.

### Analysis

Analysis will include calculation of the effect size of TECC to reduce symptoms related to stress, anxiety, and depression. Analysis will also focus on assessing association between baseline factors, race, language, and education, as well as dynamic factors like working alliance and technology engagement patterns with changes in symptoms and use and adherence to the TECC protocol. We will assess relationships between these factors and clinical changes using generalized linear models and multiple regression analyses. Tests for dropout effects will be performed to see if outcome and covariate measures are associated with differences in engagement. If there are significant dropout effects, a logistic dropout probability model will be fit using the significant dropout outcomes and covariates measured at the start of the stage, and inverse probability weighting will be used with these model probabilities to account for dropout in each of the models. The age-matched control group will be used to compare changes related to clinical scores and calculate effect sizes using means and SDs.

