Stage 1 “Creating the Clinical Foundation”: This stage will allow participants to learn and practice shared decision-making by cocreating treatment goals, identifying thought patterns, and identifying coping skills and defense mechanisms. The goal of this stage is for participants to develop a broad understanding of their thoughts and behaviors while beginning to identify strengths and need areas. Participants will also be introduced to clinical language and definitions for shared language to be established.Stage 2 “Building Clinical Skills”: Expanding from the skills learned in stage one, this stage will focus on teaching and practicing cognitive defusion and behavioral activation techniques. The goal for this stage is to expose participants to practical therapeutic skills that can be used across many situations and symptom management.Stage 3 “Solidifying Clinical Gains”: This stage introduces participants to mindfulness techniques, a diary card–like model, and patient activation and empowerment skills. The purpose of this stage is to ensure participants grasp all technical skills and clinical language reviewed throughout treatment to make informed autonomous decisions regarding treatment preferences.

This yearlong study will follow a prospective longitudinal cohort design where all participants will receive the same treatment and smartphone interventions. Based on our own Digital Clinic pilot data, we hypothesize participants will report a treatment response rate—defined as 50% symptom reduction—of improvements in anxiety and depression within the 8 weeks of treatment compared to their initial baseline. We also hypothesize that both rates of app engagement out of sessions, as well as therapeutic alliance measured during sessions, will be correlated with clinical improvements and suggest a mechanism of action for TECC. Furthermore the study will test the feasibility of providing technology-enabled mental health care within an outpatient clinical setting via virtual telehealth visits, explore the linguistic and cultural appropriateness of the smartphone app (mindLAMP) used in the study, and analyze the symptom changes of anxiety and depression for all study participants.

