## Methods

### Study

The study will take place at Beth Israel Deaconess Medical Center (BIDMC), a Harvard affiliated teaching hospital in Boston, Massachusetts. The care team will include a psychiatrist, social worker, and digital navigator. The psychiatrist and social worker will provide clinical treatment, education, and support for all participants. The digital navigator, as previously discussed, will be available for technology support and mindLAMP training to other care team members and research participants.

For this study, 50 participants will be enrolled and will not be financially compensated for their participation in TECC. Given the success of the pilot Digital Clinic program, including 50 participants is feasible and necessary to collect a diverse sample and see significant effects of different techniques on clinical assessments of depression and anxiety. This study will be open to any adult (18 years or older) who is interested in using smartphone technology to augment their mental health care. Participants are required to meet the criteria for either mild to moderate depression or anxiety as measured on the Patient Health Questionnaire-9 (PHQ-9) or Generalized Anxiety Disorder-7 (GAD-7) scale. Participants must have daily access to a smartphone, be willing to download the mindLAMP app, use their smartphone for mental health care (both in and outside of session time), and be open to learning about an array of clinical modalities (dialectical behavior therapy [DBT], cognitive behavioral therapy [CBT], short psychodynamic therapies). For participants who do not own a smartphone, the care team will help individuals sign up for a free phone through the US Federal Government’s Project Lifeline if they are eligible. Participants must also be affiliated with a BIDMC or Beth Israel Lahey Health provider and be available for eight clinical sessions (telehealth) over the course of 2-4 months. Until the Spanish language version of the mindLAMP app has been properly vetted, participants must be able to read, write, and communicate in English at an eighth grade level. Recruitment efforts for TECC include digital flyers and brief informational sessions for referring providers.

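### Engagement and alliance correlations are to suggest a mechanism, but motivation, measured before every visit, is not named or committed to as a covariate in those models

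*Protocol article*

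**What the plan says.** All statements are in the protocol article.

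- **Design (Introduction).** The study is a "prospective longitudinal cohort design where all participants will receive the same treatment and smartphone interventions". Engagement and alliance are therefore observed, not allocated.
- **Hypothesis (Introduction).** Engagement outside sessions and alliance during sessions "will be correlated with clinical improvements and suggest a mechanism of action for TECC".
- **Data (Study Measures).** The surveys before each session include "a patient motivation scale, to asses participants commitment to change through treatment". Timing: "Prior to each clinical visit, participants will briefly meet with a research assistant who will provide participants with a secure link (via REDCap) to weekly" questionnaires. A value before session one should therefore exist. The alliance scale starts only after session one.
- **Models (Analysis).** The factors are "baseline factors, race, language, and education, as well as dynamic factors like working alliance and technology engagement patterns", and the method is: "We will assess relationships between these factors and clinical changes using generalized linear models and multiple regression analyses". Motivation is not mentioned there, and no other section gives it a role in the analysis.
- **Size (Study).** "For this study, 50 participants will be enrolled". The reason given is feasibility and diversity of the sample, without a significance level, power or effect size.

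**The concern.** Commitment to change is a plausible common cause of all three quantities in the mechanism hypothesis: app use, alliance rating and improvement. If it drives all three, engagement and alliance will correlate with improvement even when neither does anything, and the predicted pattern will appear.

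Nothing else in the Analysis section deals with this. The inverse probability weighting is for dropout and does not address confounding among those who stay. The matched comparison group is there to compare changes in clinical scores, and nothing suggests that it supplies TECC engagement or alliance data. Adjusting for baseline symptom severity would not remove the problem, because motivation is a different variable.

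At stake is the reading of a stated hypothesis. The Results section says that the findings will be used to support or adapt the care model and to build training resources. A correlation produced by motivation could then be taken as a reason to push app use. The primary symptom outcomes are not affected.

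**Working it through.** The sample size of 50 comes with no design inputs, so there is no figure of the plan to reproduce. The check asks how often motivation alone would give the predicted result.

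**Inputs**
- n = 50 (Study section).
- Two-sided 5% test: assumed, as the article states no level.
- a = correlation of motivation with engagement (or alliance), and b = correlation of motivation with improvement. The article gives neither. Assumed a = b = 0.3, 0.4 and 0.5.
- Engagement has no effect on improvement (the null hypothesis of interest).

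**Step 1: induced correlation.** If motivation is the only link, corr(engagement, improvement) = a × b.
- 0.3 × 0.3 = 0.09
- 0.4 × 0.4 = 0.16
- 0.5 × 0.5 = 0.25

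The smallest |r| that is significant at n = 50 is 0.279.

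**Step 2: chance of a significant unadjusted result.** By Fisher's z, s = atanh(r) × √(50 − 3), and the rejection rate is Φ(s − 1.96) + Φ(−s − 1.96).

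| a = b | induced r | s | rejection rate |
|---|---|---|---|
| 0.3 | 0.09 | 0.0902 × 6.856 = 0.619 | 9.5% |
| 0.4 | 0.16 | 0.1614 × 6.856 = 1.106 | 19.8% |
| 0.5 | 0.25 | 0.2554 × 6.856 = 1.751 | 41.7% |

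Simulation with 20,000 replicates gives 9.6%, 19.8% and 42.6%. A separate run of 5,000 gives 9.8%, 20.2% and 40.8%. The differences are simulation error.

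Beyond the main range, a = b = 0.6 and 0.7 give 73.4% and 95.7%. Motivation alone produces a significant result more often than not only if both links are above about 0.5.

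**Step 3: adjusted for motivation, error-free scale.** The numerator of the partial correlation is ab − a × b = 0. The simulated rejection rate is about 5% throughout.

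**Step 4: adjusted, reliability 0.8 (assumed).** The observed score correlates a√0.8 and b√0.8 with the other two variables. With a = b, the partial correlation is (a² − 0.8a²) / (1 − 0.8a²) = 0.2a² / (1 − 0.8a²).
- a = 0.3: 0.018 / 0.928 = 0.019; simulated rejection 4.9%
- a = 0.4: 0.032 / 0.872 = 0.037; 5.8%
- a = 0.5: 0.050 / 0.800 = 0.063; 6.8%

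At a = b = 0.6 and 0.7, adjustment with the imperfect scale still leaves 10.6% and 19.7%.

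**The case against.** **The list is open.** The phrase on baseline factors may be general, and the dynamic factors are introduced as examples. A motivation score before session one could count as a baseline factor, and a weekly one as a dynamic factor. This stands: a reader might infer that motivation is excluded from the regressions, and the text does not say so. But listing motivation as one more factor would only promise its own association with change. Confounding is reduced only if motivation is in the same model as engagement or alliance, and the article does not commit to that.

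**Covariate lists belong in the SAP.** True in general. The point here is narrower: the article itself states how the correlation will be read and names factors for the models, without the measured variable most directly relevant to that reading.

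**The article claims little.** It says that the correlations will suggest a mechanism, and the Analysis section speaks of association. Engagement and alliance are secondary outcomes in the Abstract. This also stands. A reader might infer that the trial sets out to confirm a mechanism, and the wording is weaker than that.

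**The size is assumed.** No correlation with motivation is given anywhere. Entry requires willingness to use a smartphone for care (Study section), which may narrow the range of motivation and weaken both links. At 0.3 the inflation is modest.

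**Adjustment is not a cure.** The scale is given no name or reference, so its reliability is unknown. Other confounders may exist, and early improvement can itself raise engagement and alliance. It would be wrong to infer that one covariate restores a valid test of mechanism.

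**Conclusion.** The point holds as one about the chosen model and the reading of its result. The article lets correlations of self-selected engagement and alliance suggest a mechanism, while a plausible common cause that it measures before each visit has no committed place in the models. It does not show that motivation will be left out.

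The size is conditional. With no effect of engagement, n = 50, a two-sided 5% test and motivation correlated 0.3 to 0.5 with both engagement and improvement, about 10% to 42% of trials would show a significant correlation. Adjustment lowers this to about 5% if the scale has no error and there is no other confounder, or to about 5% to 7% at reliability 0.8. The same argument applies to alliance under the same assumed correlations.

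The change is worth making because it is cheap and uses a value already collected. It affects a secondary hypothesis, not the primary symptom outcomes.

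**What to change.** In the Analysis section:

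1. Prespecify the motivation score taken before session one as a covariate in each model of symptom change on engagement or alliance.
2. Report the engagement and alliance coefficients with and without it.
3. Do not use later motivation scores as covariates in these models, because treatment may have changed them.
4. State that the score before session one is not strictly free of app exposure. By the Interventions section, participants receive the app and begin daily surveys at least one week earlier. The score does precede all clinical sessions and the first alliance rating.
5. Describe the results as associations, here and in the hypothesis in the Introduction, because adjustment does not exclude other confounders or early improvement raising engagement and alliance.

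Cost: one degree of freedom per model and no new data.
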